#### Cognitive and Affective Mindfulness Scale – Revised

Trait mindfulness is measured using the Cognitive and Affective Mindfulness Scale – Revised (CAMS-R), a 10-item self-report questionnaire. This scale uses everyday language appropriate for those with little meditation experience and is designed to capture mindfulness as a general daily experience [50]. The questionnaire comprises four domains of mindfulness (attention, present-focus, awareness and acceptance/non-judgment). Participants are asked to rate on a 4-point Likert scale how much they relate to each statement. Possible responses are 1 = rarely/not at all, 2 = sometimes, 3 = often and 4 = almost always.

Compared to other measures of mindfulness, the CAMS-R is unique in that it is related to psychological distress [51], which is highly relevant to the current study population [52].

#### Perceived Stress Scale

The Perceived Stress Scale (PSS; 10-item version) is a self-report questionnaire measuring the global perception of stress [53]. The items were designed to evaluate how unpredictable, uncontrollable and overloaded respondents find their lives. The scale has internal consistency ranging from 0.75 to 0.86 [54]. Consistent with this range, studies measuring perception of stress in people with prostate cancer [55] and breast cancer [56] had Cronbach’s *α* of 0.78 and 0.87, respectively.

#### Assessment of intervention content relevance

At the end of each week, a short questionnaire will ask participants if the weekly topic was beneficial and what aspects of the program were liked or disliked. At week 6, additional three questions ask about the overall helpfulness of the mindfulness program and feature that were the most liked or disliked.

#### Adherence tracking and meditation log

Google Analytics will be used to track participants’ online activity, including login date/times, navigation patterns, page views and duration, and features used (video, audio and document downloads). At the end of each week, a set of three questions will capture information on any use of other types of meditation unrelated to the intervention, and frequency and duration of practice. Another three questions will estimate the amount of informal practice over the past week, and the specific use of the weekly topic, using a 5-point Likert scale.

#### Controlling for existing mindfulness experience in the control group

In order to control for the potential influence of an external mindfulness-based program in the control group, participants will answer a question included in the end-of-study questionnaire about whether they have enrolled in a mindfulness-based program during the past 6 weeks.

### Sample size

We aim to enrol 75 participants over a 5-month period. The target sample size of 75 participants (50 in the intervention group, 25 in the control group) meets recommendations for pilot studies aimed at evaluating feasibility and estimating variance to inform sample size and power calculations for a main trial [57]. The 5-month recruitment period was informed by (1) screening past melanoma clinic lists for eligible patients at the cancer centre over a period of 3 months, (2) findings from a survey-based study among people with melanoma [28], and (3) an estimated 70% participation rate based on findings from online mindfulness-based pilot studies for patients with cancer [29, 58] (Fig. 1).

### Analysis plan

Descriptive statistics will be used to present participants’ characteristics. Demographic and clinical characteristics, and experience with meditation will be compared between intervention and control groups, using *t* test or Wilcoxon rank-test (for continuous variables) depending on the outcome distribution and chi-square or Fisher’s exact test (for categorical variables).

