## Abstract

**Background:**

People with a melanoma diagnosis are at risk of recurrence, developing a new primary or experiencing disease progression. Previous studies have suggested that fear of a cancer recurrence is clinically relevant in this group of patients and, if not addressed, can lead to distress. Mindfulness-based interventions have been shown to alleviate symptoms of anxiety and depression among various groups of cancer patients. Online mindfulness-based interventions have the potential to reach people unable to attend face-to-face interventions due to limitations such as cancer-related illness, transportation or time constraints. This study aims to (1) examine whether individuals with a melanoma diagnosis are willing to participate and adhere to a 6-week online mindfulness-based intervention and (2) explore potential benefits of the program on fear of cancer recurrence, worries, rumination, perceived stress and trait mindfulness to inform the design of a clinical trial.

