### Setting and recruitment process

Recruitment will take place in the melanoma outpatient clinics of a major metropolitan cancer centre in Melbourne, Australia. Patients will be identified through the melanoma outpatient database and study eligibility determined using electronic medical records.

During the follow-up consultation, clinicians will inform patients of their eligibility and will invite them to meet with the researcher at the end of the consultation to learn more about the study.

Patients will be reminded that participation is voluntary and their decision to participate or not will have no impact on their clinical care. A patient information package will be provided to each interested patient, and the researcher will follow up by telephone as agreed with patients to answer any questions related to the project.

Upon providing online consent to participate, a unique study identification number will be automatically generated for each participant. This identification number will be generated by a SSL-certified server to ensure privacy and integrity of the data and will not contain participants’ personal information. Participants will then be directed to the baseline questionnaire and upon completion will be randomised into either the intervention or the control group. Participants will also receive an email confirming the condition they are assigned to. The email for the intervention group will also comprise a URL address including the unique study identification number to access the intervention.

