### Randomisation

Participants are randomised (2:1) to the intervention or control group stratified by sex, time since treatment completion (≤12 months, >12 months), and meditation experience (yes/no). A random sequence will be generated for each one of the eight strata using block randomisation. For every three participants enrolled in each stratum, two will be allocated to the intervention group and one to the control group. Random sequences will be embedded in the online system, ensuring allocation concealment. Study personnel will not have access to the sequences and will be blind to group assignment. After randomisation, participants will be unblinded to group assignment, as the intervention does not allow for blinding. All questionnaires will be completed online, which will reduce the influence of researcher bias. Given the nature of the intervention and the context in which participants are recruited, i.e. outpatient clinic, we cannot rule out the usual risks of bias due to participants not being blinded to treatment allocation. However, in this study, all surveys will be completed online; health practitioners have no involvement in the collection or assessment of any of the trial outcomes. Unequal randomisation, where the number of participants allocated to the intervention group exceeds that in the control group, has been identified as a suitable approach in early-phase studies where the aim is to explore various dimensions of the intervention, such as patterns and frequencies of usage [34].

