#### Primary objective—feasibility

Descriptive statistics will be used to present feasibility data. The overall study feasibility will be assessed through the following measures:Proportion of people approached (target: 80%): number of people approached as a proportion of those meeting clinical eligibility. Reasons for not approaching will be summarised.Proportion of people eligible for the study (target: 65%): number of people meeting all eligibility criteria as a proportion of those approached. Reasons for non-eligibility criteria and declining participation will be summarised.Proportion of people enrolled (target: 45%): number of people completing the baseline questionnaire as a proportion of those eligible.Completion rate (target: 70%): number of participants completing the end-of-study assessment as a proportion of those enrolled. It will not be possible to capture reasons for non-completion as there will be no interaction between the researcher and participants once they are enrolled in the study.

The intervention feasibility will be assessed through the following measures:Meditation adherence rate (target: 70%): number of guided meditations listened to per week over the total number of meditation sessions scheduled (14 sessions/week)Rate of adherence to weekly sessions (target: 50%): the number of videos viewed over the total number of videos scheduled per weekEngagement with the intervention: recording website navigation patterns and features used (video, audio and document downloads)Content relevance: type of benefits experienced and aspects of the program most liked and disliked (data collected through weekly questionnaires)

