#### Secondary objectives—potential efficacy of intervention on outcome measures

To explore the potential efficacy of the intervention on any of the secondary outcomes (i.e. fear of cancer recurrence, worry, rumination, perceived stress and trait mindfulness), a linear mixed model will be fitted including group (intervention, control), time (pre, post) and the interaction group by time as fixed effects and participant as a random effect. We will additionally adjust for any characteristics or scores showing clear evidence of imbalance at baseline. All analyses will be undertaken on an intention-to-treat (ITT) basis, i.e. participants will be analysed as randomised regardless of adherence.

In addition, potential association between overall meditation time and the secondary outcome measures will be assessed in the intervention group. Weekly meditation time will be defined as the maximum between time collected from Google Analytics and time self-reported in the weekly questionnaires.

Results of this study will be prepared in accordance with the CONSORT 2010 statement: extension to randomised pilot and feasibility trials [59].

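### Significance tests between randomised arms steer covariate choice in the efficacy model, while baseline data held on everyone enrolled are given no stated use in describing who is lost

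*Protocol article*

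**What the plan says.** The opening paragraph of the *Analysis plan* states: "Demographic and clinical characteristics, and experience with meditation will be compared between intervention and control groups". The tests are t or Wilcoxon for continuous variables and chi-square or Fisher's exact for categorical ones.

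Under *Secondary objectives*, the linear mixed model has group, time and their interaction as fixed effects and participant as a random effect. The plan then adds: "We will additionally adjust for any characteristics or scores showing clear evidence of imbalance at baseline". It gives no definition of clear evidence. The tests above are the only stated means of judging it.

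*Randomisation* stratifies by sex, time since treatment completion and meditation experience. Within each of the eight strata, every three participants are split two to one.

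Under *Primary objective—feasibility*, enrolment means having completed the baseline questionnaire, and the completion rate (target 70%) is the share of those enrolled who complete the final assessment. On those who do not, it says: "It will not be possible to capture reasons for non-completion". *Study discontinuation* adds that the team cannot contact people who stop using the website.

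**The concern.** Two statements in the plan point the wrong way.

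First, a significance test of baseline characteristics between concealed randomised arms addresses a null hypothesis that is true by design. Its p-value says nothing about whether an imbalance matters, which depends on how large it is and how strongly the characteristic predicts outcome. One item named for testing, meditation experience, is a stratification factor, so its balance is largely forced. The tests would be harmless if they only decorated a table, but the imbalance rule gives them a consequence: they help choose covariates for the model behind the effect size and variance estimates that are meant to inform a larger trial.

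Second, retention is a primary outcome, and the plan rules out learning why people leave. Baseline characteristics and scores, held on every enrolled person, are then the main remaining evidence on who leaves. The article compares these characteristics only between arms. If loss is selective, the completion rate is harder to interpret for a larger trial, and so are the effect and variance estimates from those who stay.

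**Working it through.** **Inputs from the article.** Total 75, with "50 in the intervention group, 25 in the control group" (*Sample size*). Targets of 45% for enrolment and 70% for completion (*Primary objective—feasibility*). Ten characteristics in *Data collection*: sex, age, education, marital status, employment, meditation experience, stage, dates of diagnosis and treatment (counted as one), types of treatment, and time since end of treatment. Three of these are stratified, leaving seven.

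**Assumptions.** Two-sided 5% level per test and independent tests. The article states neither.

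1. *The plan's own figure.* 75 × 2/3 = 50 and 75 × 1/3 = 25, so the split reproduces. There is no power calculation to reproduce.

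2. *Chance of at least one flag among k tests*, 1 − 0.95^k:
   - k = 7 (unstratified items): 1 − 0.95^7 = 0.302, with 7 × 0.05 = 0.35 flags expected
   - k = 10 (all items): 0.401, too high here because three items are balanced by design
   - k = 12 (the seven items plus five baseline outcome scores, if these are screened in the same way): 0.460
   - range for k = 5 to 15: 0.226 to 0.537

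3. *What the screen lets through.* In SD units, the standard error of a difference between arms is √(1/50 + 1/25) = 0.245. The flagging threshold is about 1.96 × 0.245 = 0.48 SD. A smaller imbalance passes unflagged however strongly the characteristic predicts outcome.

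4. *Returners against non-returners.* 75 × 0.70 = 52.5, so about 53 against 22. For a characteristic held by half, the 95% half-widths are:
   - overall: 1.96 × √(0.25/53 + 0.25/22) = 1.96 × 0.127 = 0.249, about ±25 points
   - intervention arm at the same rate (35 against 15): 1.96 × √(0.25/35 + 0.25/15) = 0.302, about ±30 points
   - control arm (17.5 against 7.5): 1.96 × √(0.25/17.5 + 0.25/7.5) = 0.428, about ±43 points

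   For a continuous score, the overall half-width is 1.96 × √(1/53 + 1/22) = 0.50 SD. The difference detectable with 80% power is about 0.71 SD.

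5. *Enrolled against eligible but not enrolled.* 75/0.45 = 167 eligible, leaving about 92. The half-width is 1.96 × √(0.25/75 + 0.25/92) = 0.152, about ±15 points. This is adequate for description, but only for items that may lawfully be held on people who did not consent.

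**The case against.** The strongest reply is that little turns on the tests. Feasibility is assessed descriptively and no feasibility target depends on a baseline p-value. Clear evidence of imbalance is not defined as a p-value. The tests as written also do not cover the outcome scores that the adjustment rule includes. All of that is true. The link between test and covariate is an inference, but no other criterion is offered, and a rule applied after seeing the data is still chosen by chance imbalance.

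A related reply concerns size, and it also stands in part. In this model, with both measurements present, a baseline covariate entered only as a main effect drops out of the group-by-time contrast. It can move that contrast through incomplete pairs, about 30% of participants at the completion target, or if it is entered with a time interaction. It also changes the between-participant variance. The article does not say how covariates enter, so the shift cannot be computed.

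A third reply is that attrition tables often sit in a full analysis plan that is not shown. This weakens any complaint about absence alone. It does not touch the tests and the adjustment rule, which are stated.

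A reader might go further and infer that the study cannot say who is willing to take part or stay, or that it must compare enrolled with non-enrolled people. The documents do not support that. The first aim is to "examine whether individuals with a melanoma diagnosis are willing to participate and adhere to a 6-week online mindfulness-based intervention", and the planned rates, each with a denominator and target, answer whether. Reasons for not approaching people, for ineligibility and for declining are to be summarised, which serves the stated interest in barriers to recruitment. Nor are data on non-enrolled people clearly available. Records are read for screening ("Patients will be identified through the melanoma outpatient database and study eligibility determined using electronic medical records"), but *Data collection* takes clinical data with participants' consent, and demographics and meditation experience are obtained at baseline, after consent.

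**Conclusion.** The point holds in a limited form. The stated between-arm tests have no inferential value, and the imbalance rule lets chance help choose the efficacy model. The chance of at least one flag is about 30% for seven unstratified characteristics, and 23% to 54% for 5 to 15 tests, assuming a 5% level and independence. Correlated characteristics would change these figures. How far an estimate would move is not known.

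The retention part rests on the plan's own statement that reasons for loss cannot be obtained, and on baseline data existing for everyone enrolled. Describing who is lost is worthwhile but imprecise, at about ±25 points overall and much wider within arms. It cannot support tests or firm claims about predictors of loss.

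Neither part undermines the feasibility rates. This should be corrected before analysis, but it is not a fatal flaw.

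**What to change.** 1. In the *Analysis plan*, replace the between-arm tests with summary statistics by arm and no p-values.
2. Under *Secondary objectives*, replace the imbalance rule with covariates named in advance, including the three stratification factors, and state how they enter the mixed model.
3. Add a descriptive table of final-survey returners against non-returners on baseline characteristics and scores, with confidence intervals for the overall differences. Show counts by arm as description only. If a full analysis plan already contains this table, a reference to it is enough.
4. Optionally, summarise enrolled against eligible but not enrolled people on de-identified items already seen at record screening, if ethics approval permits.

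The first three changes need only wording and one extra table from data already collected. The cost is giving up the freedom to adjust for an unexpected imbalance in the main model. Such an adjustment can still be reported as a labelled sensitivity analysis. The fourth needs a short screening log and possibly an ethics amendment.

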#### Primary objective—feasibility

Descriptive statistics will be used to present feasibility data. The overall study feasibility will be assessed through the following measures:Proportion of people approached (target: 80%): number of people approached as a proportion of those meeting clinical eligibility. Reasons for not approaching will be summarised.Proportion of people eligible for the study (target: 65%): number of people meeting all eligibility criteria as a proportion of those approached. Reasons for non-eligibility criteria and declining participation will be summarised.Proportion of people enrolled (target: 45%): number of people completing the baseline questionnaire as a proportion of those eligible.Completion rate (target: 70%): number of participants completing the end-of-study assessment as a proportion of those enrolled. It will not be possible to capture reasons for non-completion as there will be no interaction between the researcher and participants once they are enrolled in the study.

The intervention feasibility will be assessed through the following measures:Meditation adherence rate (target: 70%): number of guided meditations listened to per week over the total number of meditation sessions scheduled (14 sessions/week)Rate of adherence to weekly sessions (target: 50%): the number of videos viewed over the total number of videos scheduled per weekEngagement with the intervention: recording website navigation patterns and features used (video, audio and document downloads)Content relevance: type of benefits experienced and aspects of the program most liked and disliked (data collected through weekly questionnaires)

#### Secondary objectives—potential efficacy of intervention on outcome measures

To explore the potential efficacy of the intervention on any of the secondary outcomes (i.e. fear of cancer recurrence, worry, rumination, perceived stress and trait mindfulness), a linear mixed model will be fitted including group (intervention, control), time (pre, post) and the interaction group by time as fixed effects and participant as a random effect. We will additionally adjust for any characteristics or scores showing clear evidence of imbalance at baseline. All analyses will be undertaken on an intention-to-treat (ITT) basis, i.e. participants will be analysed as randomised regardless of adherence.

In addition, potential association between overall meditation time and the secondary outcome measures will be assessed in the intervention group. Weekly meditation time will be defined as the maximum between time collected from Google Analytics and time self-reported in the weekly questionnaires.

Results of this study will be prepared in accordance with the CONSORT 2010 statement: extension to randomised pilot and feasibility trials [59].

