### Aims and objectives

The overall aim of the study is to examine the feasibility and acceptability of an online mindfulness-based program among people who have completed treatment for melanoma.

The primary objective of the study will be to assess the feasibility of conducting a larger scale randomised control trial by evaluating:Overall recruitment, retention and questionnaire completion ratesAdherence to, and usability and acceptability of, the online program

The secondary objectives will be to assess the potential benefit of the intervention on fear of cancer recurrence, worry, rumination, perceived stress and trait mindfulness compared to a usual-care group and to provide effect size and variance estimates for these outcomes to inform the design of a larger clinical trial.

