## Methods/design

### Design

The development of the study protocol followed the SPIRIT (Standard Protocol Items: Recommendations for Interventional Trials) guidelines [30] (Additional file 1). The description of the intervention followed the TIDieR (Template for Intervention Description and Replication) guidelines [31] (Additional file 2).

This study is a single-centre, randomised controlled pilot study. The control group will continue to receive care from their treatment centre as usual, while participants in the intervention group will receive access to a 6-week online mindfulness program as well as their usual care. The groups will be compared to assess the potential effect of the intervention on a series of outcome measures. Measurements will take place at baseline (i.e. before randomisation) and at the end of the study (i.e. 6 weeks after randomisation). In the intervention group, participant engagement with, and usability and acceptability of, the program will be assessed weekly through a short questionnaire. The overall design and participant flow through the trial is illustrated in Fig. 1.

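### The secondary-outcome mixed model leaves baseline means free by group, so the planned imbalance adjustment hardly reaches the treatment estimate and precision is lost against a baseline-adjusted analysis

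*Protocol article*

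**What the plan says.** Under Secondary objectives in the Analysis plan, the protocol says of each secondary outcome that "a linear mixed model will be fitted including group (intervention, control), time (pre, post) and the interaction group by time as fixed effects", with "participant as a random effect". It continues: "We will additionally adjust for any characteristics or scores showing clear evidence of imbalance at baseline". It names no covariate-by-time term, no common baseline mean and no model for the 6-week score alone.

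The Design section fixes the visits: "Measurements will take place at baseline (i.e. before randomisation) and at the end of the study (i.e. 6 weeks after randomisation". Baseline is therefore one of the two responses in the model, and the group main effect lets the two groups have different means at a visit that comes before randomisation.

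Aims and objectives gives the purpose of these analyses, besides exploring benefit: "to provide effect size and variance estimates for these outcomes to inform the design of a larger clinical trial".

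**The concern.** Two things look wrong in the model as written.

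- **The adjustment is aimed at a term that it mostly cannot reach.** With two visits and a free group effect, the treatment effect is a within-person contrast. A main-effect covariate acts between persons. A team that sees an imbalance and adjusts for it would believe that it had been dealt with, when the estimate has hardly moved.
- **Precision is given away.** Randomisation makes the expected baseline means equal. A model that estimates a separate baseline mean in each group does not use that fact.

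At stake are the effect estimates handed to the main trial. They come from a small sample with 2:1 allocation, where chance imbalance is likely and information is scarce.

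**Working it through.** **Inputs.** Model and adjustment rule: Secondary objectives. Two visits: Design. Sample: "The target sample size of 75 participants (50 in the intervention group, 25 in the control group". Follow-up: "Completion rate (target: 70%): number of participants completing the end-of-study assessment as a proportion of those enrolled", which gives 50 × 0.7 = 35 and 25 × 0.7 = 17.5 completers. The protocol gives no SD, effect size or pre-post correlation r, so it has no figure to reproduce. Here r is an assumption, shown from 0.3 to 0.9. Results are in SD units, with equal SDs at the two visits.

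**Step 1: algebra.** Write the stated model with a time-constant covariate x as

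Y(i,t) = μ + α·g(i) + τ·t + δ·g(i)·t + γ·x(i) + u(i) + e(i,t), with t = 0, 1.

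Then Y(i,1) − Y(i,0) = τ + δ·g(i) + e(i,1) − e(i,0). Both γ·x(i) and u(i) drop out. With both visits observed, the estimate of δ is the difference between groups in mean change, with or without x.

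**Step 2: check by REML on simulated 50:25 data with an imbalanced characteristic, complete pairs.**

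| r | Difference in mean change | Stated model | + characteristic | + own baseline score | + characteristic × time |
|---|---|---|---|---|---|
| 0.3 | −0.422302 | −0.422302 | −0.422302 | −0.422302 | −0.507 |
| 0.5 | −0.280924 | −0.280924 | −0.280924 | −0.280924 | −0.203 |
| 0.7 | −0.558189 | −0.558189 | −0.558189 | −0.558189 | −0.636 |

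Only the time interaction moves the estimate. Adding the outcome's own baseline leaves the estimate alone but lowers the model SE (0.316 to 0.293 at r = 0.3). That gain is false: the same value stands on both sides of the equation.

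**Step 3: incomplete pairs.** With about 30% of 6-week values removed at random, the main-effect covariate does move the estimate: −0.375 to −0.500 at r = 0.3, −0.329 to −0.316 at r = 0.5, and −0.577 to −0.598 at r = 0.7. Over 200 simulated data sets (50:25, 70% completion, r = 0.5, covariate imbalanced by 0.6 SD) the median shift was 0.03 SD and the 90th percentile 0.09 SD. The size depends on how strongly the covariate predicts the outcome. The shift arises only because participants with a baseline score alone add between-person information.

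**Step 4: precision.** With n randomised and c completers per group, large-sample variances are

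- stated model: (1−r²)(1/c₁+1/c₀) + (1−r)²(1/n₁+1/n₀)
- baseline-adjusted: (1−r²)(1/c₁+1/c₀)

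With complete data the first reduces to 2(1−r)(1/n₁+1/n₀), so the ratio is (1−r²)/[2(1−r)] = (1+r)/2.

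| r | Ratio, complete data | Monte Carlo, 20,000 runs | Ratio, 70% completion (35 v 17.5) |
|---|---|---|---|
| 0.3 | 0.65 | 0.665 | 0.73 |
| 0.5 | 0.75 | 0.759 | 0.81 |
| 0.7 | 0.85 | 0.863 | 0.89 |
| 0.9 | 0.95 | 0.967 | 0.96 |

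Worked example for 35 v 17 completers at r = 0.5: 1/35 + 1/17 = 0.0874 and 1/50 + 1/25 = 0.06.

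- Baseline-adjusted: 0.75 × 0.0874 = 0.0655; half-width 1.96 × √0.0655 = 0.50.
- Stated model: 0.0655 + 0.25 × 0.06 = 0.0805; half-width 1.96 × √0.0805 = 0.56.

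At r = 0.7 the same steps give 0.0446 and 0.0446 + 0.09 × 0.06 = 0.0500, so half-widths of 0.41 and 0.44.

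With unequal SDs and complete data, the two variances differ by (SD_pre − r·SD_post)² times (1/n₁+1/n₀). This is never negative, so the direction does not depend on the equal-SD assumption.

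**The case against.** The strongest reply is that group, time, group-by-time and a random participant effect form a standard, valid analysis of a two-visit randomised trial, so that this is a preference between sound methods on outcomes that decide nothing. Validity stands. The difference in mean change is unbiased over repeated randomisation, and a reader who infers that the stated model is biased by chance imbalance would go further than the documents allow. But the alternative uses the same data and costs nothing, so there is no trade-off to defend.

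A second reply is that the adjusted result will not equal the unadjusted one in practice. This is right. The protocol targets 70% completion, and an intention-to-treat mixed model keeps participants with a baseline score only. Identity holds for complete pairs; beyond them the shift is usually small. What survives is that the adjustment works only through incomplete pairs, which is not its purpose.

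A third reply is that the protocol does not say how covariates enter. A time interaction would change the estimate, and an analysis plan might specify one. The plain reading is a main effect, and the free group effect is stated outright, so the precision point holds either way.

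A fourth is that the word scores need not mean the outcome's own baseline. That stands. Five instruments are listed, and the baseline of one can coherently enter the model for another. The misspecification concerns only an outcome's own baseline.

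**Conclusion.** The point holds with limits. In complete pairs, a time-constant characteristic entered as a main effect cannot change the group-by-time estimate. With follow-up near the 70% target it changes it a little, so the planned adjustment largely does not do its job. The stated model is unbiased but has more variance than a baseline-adjusted analysis. At 70% completion the baseline-adjusted variance is about 0.73 to 0.96 of the stated model's for r from 0.3 to 0.9. With 35 v 17 completers, that narrows the 95% half-width by about 0.05 SD at r = 0.5 (0.556 to 0.502) and 0.02 SD at r = 0.7 (0.438 to 0.414). At r of 0.9 the loss is slight.

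This rests on main-effect adjustment, large-sample variances, equal SDs for the figures, and an r that the protocol does not give. The gain is modest and concerns exploratory secondary outcomes. No efficacy decision depends on it, and the primary feasibility objective is untouched. It matters because these estimates are meant to inform the main trial and the improvement is free.

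**What to change.** For each secondary outcome, replace the stated model by one of these:

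- a mixed model with a common baseline mean: time and group-by-time, no group main effect, with the stratification factors (sex, time since treatment completion, meditation experience) and their interactions with time; or
- ANCOVA of the 6-week score on group, the outcome's baseline score and the stratification factors. This is equivalent with complete data and close to it otherwise.

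Name the covariates in advance and drop their selection by observed imbalance. In a mixed model, a covariate meant to adjust the treatment effect should enter with its time interaction. State that an outcome's own baseline is not added as a covariate to a model in which it is also a response.

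The cost is a change of wording. Baseline scores and stratification factors are already collected, and no new data, software or participants are needed.
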